#### Risk Mitigation

Along with the overall waiver of consent, a waiver of parental consent was approved for participants aged 14 to 17 years, as the protocol was designed for a subject population (here, SGM adolescents seeking readily available DMH resources via MHA’s platform) for which parental permission is not a reasonable requirement to protect this study subsample (45 CFR 46.408(c)). Generally, adolescents represent approximately 59% of MHA’s SGM visitors. In alignment, as of April 13, 2026, 52% (2004/3878) of study participants were SGM visitors aged 14 to 17 years. Including this user population is critical to understanding and optimizing the engagement behaviors of MHA’s SGM visitors, generally, and for this priority subpopulation. Adolescent-parental relational and communication issues are often cited as the main barriers to mental health care for SGM adolescents [51]. Besides disrupting natural engagement, requiring parental consent may cause safety concerns for those not ready to disclose their sexual or gender identity [52-54] or for those seeking DMH services due to relational concerns with their parents. The lower cutoff age of 14 years was chosen, as these adolescents represent high school–aged youth whom past research shows have similar health literacy as adults [55] and sufficient maturity and rational decision-making to self-consent to health and mental health care [56].

#### Confidentiality

MHA collects engagement data and optional demographic survey responses as part of standard operations. MHA’s privacy policy provides visitors with information about how data are collected, stored, and shared (Multimedia Appendix 1). IP addresses are recorded and stored indefinitely in MHA’s server access logs but are not processed to identify visitors. MHA will have access to participant identifiers, including IP addresses and ZIP codes or email addresses, if provided by visitors as part of the optional demographic survey. UW researchers will not have access to any of these direct identifiers as they are removed from datasets before transmission from MHA to UW via a secure Box account. IP addresses, specifically, are hashed using an MD5 algorithm. This process creates an indirect identifier that cannot be reversed to recover the original IP address. MHA’s procedures for data cleaning, including deidentification procedures, have been published elsewhere [37]. The deidentified data will be stored on UW servers in accordance with the University’s data security requirements.

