### Trial Setting

MHA’s Online Screening Program is a web-based program that provides access to free, confidential, and scientifically validated screening tools. Information gathered from the screening can help connect MHA visitors to resources, including articles about mental health and interactive self-help tools. This trial will enroll eligible visitors who access the PHQ-9 via MHA’s Online Screening Program during the trial period.

Engagement with MHA will be examined naturally. Data for visitor sessions will be captured passively through MHA’s website analytics system. Consistent with prior MHA research, a session is defined as activity on the MHA website from a unique IP address, bounded by 30 minutes of inactivity. Visitors with ≥30 minutes of inactivity are considered to have disengaged.

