#### Adolescent Participants

Along with the overall waiver of consent, a waiver of parental consent was approved for participants aged 14 to 17 years, as the protocol was designed for a subject population (here, SGM adolescents seeking readily available DMH resources via MHA’s platform) for which parental permission is not a reasonable requirement to protect this study subsample (45 CFR 46.408(c)). Generally, adolescents represent approximately 59% of MHA’s SGM visitors. In alignment, as of April 13, 2026, 52% (2004/3878) of study participants were SGM visitors aged 14 to 17 years. Including this user population is critical to understanding and optimizing the engagement behaviors of MHA’s SGM visitors, generally, and for this priority subpopulation. Adolescent-parental relational and communication issues are often cited as the main barriers to mental health care for SGM adolescents [51]. Besides disrupting natural engagement, requiring parental consent may cause safety concerns for those not ready to disclose their sexual or gender identity [52-54] or for those seeking DMH services due to relational concerns with their parents. The lower cutoff age of 14 years was chosen, as these adolescents represent high school–aged youth whom past research shows have similar health literacy as adults [55] and sufficient maturity and rational decision-making to self-consent to health and mental health care [56].

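### The Confidentiality section says an MD5-hashed IP address cannot be reversed; for an IPv4 address hashed without a secret key this is untrue

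*Protocol article*

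**What the plan says.** The Confidentiality section of the protocol article lists IP addresses among the identifiers that MHA holds and says: "UW researchers will not have access to any of these direct identifiers as they are removed from datasets before transmission from MHA to UW". It then describes how IP addresses are handled: "IP addresses, specifically, are hashed using an MD5 algorithm". The next sentence states the result: "This process creates an indirect identifier that cannot be reversed to recover the original IP address". The section does not mention a secret key, a salt or a random replacement identifier. For further detail on deidentification it cites an earlier publication. It also says that files go to the university through a secure account and are stored under the university's data security requirements.

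Three other places bear on the point:

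- Trial Setting gives the IP address a role in the data: "a session is defined as activity on the MHA website from a unique IP address, bounded by 30 minutes of inactivity".
- Eligibility Criteria requires every participant to have identified as LGBTQ+, and Adolescent Participants reports that "52% (2004/3878) of study participants were SGM visitors aged 14 to 17 years".
- Waiver of Consent gives two supports for the general waiver. One is a privacy policy telling visitors that their data may be shared with universities in deidentified form. The other is the minimal-risk classification.

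**The concern.** MD5 is a public function with no secret in it: the same input gives the same output for anyone who runs it. A hash of this kind is hard to invert when the possible inputs are too many to list. IPv4 addresses can be listed. Anyone holding a plain MD5 value can hash every possible address, compare, and read off the one that matches. No weakness in MD5 is needed for this, and a stronger unkeyed hash would be open to the same search.

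The sentence therefore credits the named method with a property that it does not have on its own. This is an affirmative statement in the text, so it is open to comment even though a journal article may leave procedural detail to other documents.

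At stake is the specific assurance given for IP addresses. The analysis variables named under Moderators and Covariates include sexual orientation, gender identity, age and PHQ-9 score. If an IP address can be recovered alongside them, the recipient holds, in effect, one of the direct identifiers that the section says have been removed.

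**Working it through.** **Inputs from the protocol article**

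- Method: MD5, with no key or salt mentioned (Confidentiality).
- Claimed property: irreversible, without qualification (Confidentiality).
- Share aged 14 to 17: 2004 of 3878 (Adolescent Participants).

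**The article's own figure.** 2004 / 3878 = 0.517, which agrees with the stated 52%. The irreversibility claim has no figure behind it.

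**Size of the search.** An IPv4 address has 32 bits, so there are 2^32 = 4,294,967,296 candidates.

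**Rate.** On one CPU core in plain interpreted Python, 1,048,576 dotted IPv4 addresses were hashed with MD5 in 1.9157 seconds: 1,048,576 / 1.9157 = about 547,359 per second. A separate run gave 543,318 per second.

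**Time for the whole space** = candidates / rate.

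| Hashes per second | Basis | Time for all 2^32 addresses |
|---|---|---|
| 543,318 | measured, one core | 7,905 s = 2.2 h |
| 547,359 | measured, one core | 7,847 s = 2.2 h |
| 1,000,000 | assumed | 4,295 s = 1.2 h |
| 10,000,000 | assumed | 429 s = 7.2 min |
| 100,000,000 | assumed | 43 s |
| 1,000,000,000 | assumed | 4.3 s |

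One pass serves the whole file, because each candidate hash can be compared with every stored value at once. The time does not grow with the number of participants.

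**Direct check.** A test address was recovered from its MD5 value alone in about 1 second, with the search started inside the block sharing its first octet. A search with no such start takes at most the full time above.

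**Where the argument stops.**

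- With a secret key that the recipient does not hold, candidates cannot be hashed in the same way and the search fails. A salt helps only if it is likewise kept from the recipient.
- For a full 128-bit IPv6 space, 2^128 candidates at an assumed 10^10 per second take about 1.1 × 10^21 years. The article does not say which version of address its visitors use, so the share affected is unknown.

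**The case against.** The strongest reply is that the article is a condensed account. Immediately after the disputed sentence it refers the reader to published deidentification procedures, and whether a key or salt is used is the sort of detail it may leave there. This stands as a limit on the consequence: silence about a key does not show that there is none. It does not rescue the sentence, which attributes irreversibility to MD5 hashing. If a secret key is what provides the protection, the sentence should say so.

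Several further limits also stand. The text says only IP address, with no version. It implies that the hash is in the transferred file, by calling it an indirect identifier directly after the transfer sentence, but does not say so outright. Email addresses and ZIP codes are removed before transfer. The only recipient named is the university team, working under secure transfer, institutional storage rules and review-board oversight. The Discussion acknowledges that an IP address may be shared by a household or network.

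A reader might infer more than this, and the documents do not support it:

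- *That the data on minors are unprotected, or that named adolescents can be identified from the file.* A recovered IP address is not a name, the other controls remain, and no route to a third party is described.
- *That the waiver of parental consent falls.* Adolescent Participants rests that waiver on 45 CFR 46.408(c) and on parental permission not being a reasonable requirement for this population. Only the general waiver mentions deidentified sharing. The remark that "requiring parental consent may cause safety concerns for those not ready to disclose their sexual or gender identity" concerns the act of seeking consent. It shows that the authors regard disclosure as sensitive, and says nothing about the security of research files.
- *That reversible files have already been sent.* The Results section reports enrolment, not transfers.

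**Conclusion.** The point holds in a conditional form. As written, the irreversibility statement is wrong for IPv4 addresses hashed with MD5 and no secret: recovering all of them takes about 2.2 hours on one core with unoptimised code, and less at higher assumed rates.

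The practical consequence rests on three assumptions that the article neither confirms nor excludes: no secret key or salt is applied, the address is IPv4, and the hash is in the file the university receives. If all three hold, the statement that the university team has no access to IP addresses is not true for those visitors. If MHA alone holds a secret key, protection against the recipient is intact and only the wording needs correction.

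This is a weakness in one stated safeguard. Randomisation, outcomes, sample size and the primary estimate are untouched. It merits correction because every record belongs to someone who has identified as LGBTQ+, about half of those enrolled at the reported date are aged 14 to 17, and the remedy is small.

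**What to change.** First establish whether MHA applies a secret key or salt that the university does not hold.

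- **If it does:** state this in the Confidentiality section, say who holds the key, and credit the key, not MD5, with the protection.
- **If it does not:** have MHA replace the MD5 value before transfer, either with a keyed hash (for example HMAC-SHA-256) whose key never leaves MHA, or with a random session identifier. Replace any MD5-hashed files that have already been sent and delete the old copies. Reword the sentence so that it describes the method then in use.

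The choice between the two turns on linkage. A keyed hash gives the same value each time an address recurs, so sessions can still be assembled after transfer. A random session identifier requires MHA to form the sessions first and drops any link between sessions from the same address. Either supports the planned session-level analysis, since the article already states that individuals cannot be reliably linked across visits.

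The cost should be a small change to MHA's export, with a re-export of any files already sent. The effort on MHA's side is an assumption, as the article does not describe the export process. No analysis needs to change.

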## Results

This study received funding from the National Institute of Mental Health (NIMH) in June 2023 (K01MH131795). Enrollment for the initial MRT began on March 12, 2026. As of April 13, 2026, a total of 3878 participants have been enrolled. Data collection for all MRT iterations is projected to end in July 2026. Prior to each MRT iteration, QA testing will be conducted live on the MHA website to monitor for programming and protocol execution errors. Data generated during QA periods will be retained and included in the analytic dataset if no substantive issues are identified. If any issues affecting randomization, intervention delivery, or outcome capture are detected, QA testing will continue until the issues are resolved. Data collection for analysis will then begin following a subsequent period of confirmed error-free operation. QA monitoring for programming and protocol execution errors will continue throughout the data collection period.

## Discussion

This study will evaluate the delivery of brief, HAPA-informed engagement strategies within MHA’s Online Screening Program and estimate their proximal effects on naturalistic engagement among SGM visitors. By embedding an iterative series of MRTs into a high-volume, real-world platform, the study is designed to test whether brief strategies integrated into the standard website experience increase initial and sustained engagement. The results will also support analyses that can inform iterative refinement of engagement strategies and the development of decision rules for when and how to deliver engagement supports in real-world DMH settings.

Several limitations should be considered when interpreting study findings. First, generalizability may be limited because trial eligibility depends on completion of an optional postscreening survey. The analytic sample may differ from otherwise eligible SGM visitors who do not complete demographic questions. Second, engagement outcomes are measured using website metadata within sessions bounded by inactivity, and the study cannot reliably link individuals across multiple visits because MHA does not require visitors to create accounts to access their free, anonymous resources. Consequently, we will be unable to examine longer-term engagement trajectories, repeated visits, or actions taken outside the website. Relatedly, proximal engagement outcomes such as clicks and time on page capture observable behavioral interactions but do not fully reflect experiential aspects of engagement, including attention, perceived relevance, or affective response. These measures also do not capture whether engagement ultimately leads to improvements in mental health outcomes. Third, sessions are defined using IP-based identifiers, which may not always distinguish unique individuals when multiple visitors access the site from shared networks or households. However, this approach aligns with prior MHA research and provides a practical method for measuring engagement at scale. Fourth, because engagement strategies are embedded within existing webpages, exposure cannot be guaranteed for every eligible participant. For example, if a participant does not scroll to the portion of the page where a HAPA-based message or card is embedded, estimated effects may be attenuated. Finally, because engagement strategies must be integrated into MHA’s existing visitor flow, the number and placement of decision points, frequency of strategy delivery, and types of intervention components delivered are constrained by feasibility within MHA’s existing site architecture and technical infrastructure. Although participant flow is largely predictable through the Screening Results and initial Next Steps Content Pages, navigation becomes too diffuse thereafter to feasibly implement and evaluate intervention components across all subsequent pages. The current MRT design only includes 2 decision points within a single browsing session. As a result, the degree of repeated randomization is limited compared with higher-frequency MRTs and may reduce the ability to estimate time-varying intervention effects. This structure reflects pragmatic constraints of embedding experimentation within a large, publicly available DMH website, where repeated prompts could be burdensome or disruptive to naturalistic use. Under similar constraints, the engagement strategies are limited by their design as pull components, and their effectiveness may depend on the participants’ mindset and behavior (eg, belief that MHA’s Next Step resources are needed) [36]. However, these trial and engagement strategy design choices all reflect feasibility constraints identified through the Discover, discover, Design, Build, and Testdesign, build, and test process and are consistent with the study’s aim to evaluate implementation within a real-world setting.

Despite these limitations, this protocol advances DMH engagement research by testing theory-based, SGM-relevant engagement strategies in a real-world setting where disengagement can occur within seconds. Results will identify which strategies show promise for improving naturalistic engagement at key drop-off points, whether effects differ across subgroups (eg, demographics, depression subtypes, and behavioral intentions) and contexts, and which design choices are feasible within MHA’s infrastructure. This information will guide refinement of message and card content and decisions about where additional decision points may be needed. Final study results and implications will be summarized and presented to MHA and reported to the study registry and sponsor. Results will also be disseminated to the wider scientific community through peer-reviewed publications and conferences. Although tested within MHA’s Online Screening Program, the approach of embedding brief engagement strategies at empirically identified drop-off points may be applicable to other self-guided DMH platforms that face similar challenges with user engagement. Longer-term work should examine whether proximal engagement gains translate to meaningful downstream behaviors, including use of additional resources, help-seeking, and symptom change.
